##### Other Measures

Sociodemographic data, including age, gender, academic status, and socioeconomic status.Adverse life events, collected using the Adverse Childhood Experiences Questionnaire (ACE), a 10-item self-reported scale that explores the presence of abuse and severe neglect during childhood, validated in English (62). Other psychosocial variables include living arrangements (classified into four groups: stable family, unstable family, stable institutional care, unstable institutional care), school absenteeism (partial or complete), orphan or adopted child, first-degree loss, family dysfunction (e.g., parental conflict, parental separation, divorce), and educational support.The Client Sociodemographic and Service Receipt Inventory-European Union (CSSRI-EU), a questionnaire completed by the clinician that details treatment received (including pharmacological treatments) and the type of care (such as the number of hospitalizations, outpatient services, emergency admission) (63).Satisfaction questionnaires for EMA and Stop-Cannabis will be completed at 6 months and at end-point (1 year).

#### Outcomes

Information will be collected from both EMA data and from questionnaires administered during hospitalization and follow-up.

##### Primary Outcomes

The first parameter is whether the level of adherence and the acceptability of the EMA and the Stop-Cannabis app are satisfactory in this sample. Acceptability will be assessed by measuring the dropout rate after 6 and 12 months, and usability and satisfaction *via* questionnaire in all participants and *via* face-to-face interviews with a subgroup of 10 participants. Compliance will be assessed *via* mean percentage of random prompts and predetermined assessments completed per participant. The second parameter is whether information collected using EMA *via* a mobile app is valid and reliable. Information obtained by EMA tools using the mobile app will be compared to those collected by traditional paper–pencil and clinical interview methods during the initial and follow-up assessments using correlations analysis.

##### Secondary Outcomes

(1)The prevalence of SUDs among adolescent inpatients will be assessed.(2)The clinical and psychosocial characteristics of participants with and without SUDs at baseline, including history of adverse childhood experiences, comorbid psychiatric diagnoses, and the level of functional impairment, will be compared.(3)The risk of developing SUDs among non-SUD adolescents during a 1-year follow-up period following hospital discharge will be investigated.(4)The proportion of inpatient adolescents with non-cannabis substance use at baseline whose SUDs persist at 1 year will be estimated.(5)We will explore how psychiatric symptoms could affect the pattern of substance use among SUDs participants.(6)We will assess whether specific patterns of Stop-Cannabis app use is associated with substance use outcomes at 1-year follow-up.

#### Statistical Methods

##### Primary Outcomes

Pearson correlations will be used to determine the strength of associations between daily substance use assessed by either EMA, or self-report questionnaire (e.g., CAST), or by clinician-report questionnaire (e.g., RECAP) during the clinical assessment at 6 months. Clinical reliability of the EMA will be endorsed if the correlations are statistically significantly higher than 0.70. Further analyses would be performed to estimate different aspects of reliability of the data collected in line with Perrez et al. (64). The severity of SUDs at baseline should predict the severity of substance use and the level of functional impairment at 1 year at least to comparable levels while using EMA data at baseline compared with traditional methods. Two simple linear regression models will be performed. For both the models, the dependent variable will be the severity of SUDs at follow-up; in one model, the independent variable will be the severity of SUDs based on EMA data (Model A), whereas in the other model, the variable will be severity of SUDs based on self- and clinician-report (Model B). The estimate of the independent variable is expected not to be lower in the Model A than in the Model B.

The dropout rate is expected to be less than 40% at 6 months and less than 50% at 12 months for both the EMA and traditional method, with no significant difference between methods. The results of the satisfaction survey will be estimated by analyzing the percentage of answers and the differences among the different categories using Chi-square analysis.

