## Methods and Analysis

### Selection of Participants

#### Inclusion and Exclusion Criteria

Participants will be adolescents (11–18 years old) who are hospitalized in the Department of Child and Adolescent Psychiatry at the Pitié-Salpêtrière University Hospital between September 2016 and September 2018. The participants will be assessed at baseline. According to the presence or absence of comorbid SUDs, they will be included in either the SUDs group or the control group. The SUDs group will receive the mobile apps, whereas the control group will not. Exclusive tobacco consumption is not considered to be a criterion for inclusion in the SUDs group. Inclusion to the non-SUD control group will be made according to a match with adolescents from the SUDs group (for age, gender, inpatient unit, and time of admission). Exclusion criteria include non-French speaking, those without a personal mobile phone, lack of informed consent from parents or from the adolescents, and any mental or physical problems that interfere with participation in the study (e.g., autism with very low communication abilities, severe to profound intellectual disability, severe motor disability).

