#### Sample Size

A conservative approach was adopted for this feasibility study, which emphasizes descriptive and qualitative feedback. Consequently, based on the recommendations for pilot studies (44), we plan to include 80 participants (40 cases, 40 controls) over a 2-year inclusion period. As there are around 280 inpatient admissions per year in the Department of Child and Adolescent Psychiatry, i.e., *n* = 560 potential participants contacted at baseline during the 2 years, this will represent a 14% inclusion rate. We predict that the prevalence of SUDs will be similar to that previously reported (18). A good level of compliance with EMA and Stop-Cannabis is expected, consistent with previous studies that reported high levels of adherence (up to 80%) to similar tools in adolescents with comorbid psychiatric disorders (31, 45), and in adults with associated severe psychiatric disorders (32, 46). An acceptance rate of 80% is expected in the SUD group and 50% for the control group. A 50% retention rate at 1-year follow-up is anticipated based on previous longitudinal studies among adolescents (47). In case of a lower enrollment rate, we will either continue to enroll participants during an additional year (2019) in order to reach the intended sample size or use incentives (e.g., free participation in leisure and sport activities in groups) to encourage participant enrollment.

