## Discussion

### Anticipated Results

#### Primary Objectives

A degree of correlation higher than 0.70 is expected between EMA data and data collected using other methods (particularly frequency of use), in line with prior studies (46). EMA should lead to predictions regarding the course of SUDs over the 1-year follow-up (e.g., in term of persistence, severity, and functional impairment) at least as good as other methods; that would be of interest for the clinicians involved in usual care. A high level of compliance with EMA is expected, despite the relative severity of the study sample. Based on previous studies in adolescents (45, 67), participants are expected to complete a mean of more than 70% of random signals, 50% of end-of-day assessments, and 40% of both random and end-of-day assessments. Indeed, there is good evidence that EMA can be used by patients with severe psychiatric disorders (e.g., schizophrenia) or cognitive difficulties (32, 46).

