### Limitations

Several limitations may preclude interpretation of our findings. As no control group for the Stop-Cannabis app is defined (i.e., subjects with cannabis use disorders without the intervention), the effectiveness of the Stop-Cannabis app to reduce or quit cannabis cannot be directly examined in our study. Furthermore, one other limitation is related to the lack of EMA assessments for the control group. The groups cannot be then compared with the EMA data. The authors choose to not use EMA assessment for the control group in order to avoid possible impact of the assessments on the behaviors [for a discussion about the reactivity effect of EMA, see Shiffman (25)]. The groups will receive, however at different time, a number of clinical assessments useful for the planned comparisons. As our study participants will be recruited during hospitalization in a university teaching hospital, the sample is likely to comprise youths with severe or resistant clinical profiles, which could limit the generalizability of our findings. In addition, the study design requires that only participants who own a smartphone are included, which is a risk for selection bias. Attrition biases may result from high dropout rates and low use of the app, but incentives and reminder phone calls will be employed to improve adherence. However, if important differences in baseline characteristics between adherent and non-adherent participants are detected, this will be further controlled by regression analyses. Finally, no firm conclusion about the benefit of the Stop-Cannabis application can be drawn from this study with regards to the lack of controlled randomized group.

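### Endorsing EMA only if its correlations are significantly above 0.70 asks more than 24 to 40 evaluable participants can usually show, and Pearson r cannot detect proportional under-reporting

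*Protocol article*

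**What the plan says.** Under Statistical Methods, Primary Outcomes, the protocol article plans Pearson correlations between substance use recorded by EMA and by self-report (CAST is the example) or clinician report (RECAP is the example), taken "during the clinical assessment at 6 months". The decision rule follows: "Clinical reliability of the EMA will be endorsed if the correlations are statistically significantly higher than 0.70". The same section promises further reliability analyses and a comparison of two regression models. Neither is made part of the endorsement rule.

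Under Sample Size, "we plan to include 80 participants (40 cases, 40 controls) over a 2-year inclusion period". The number rests on pilot-study recommendations: "A conservative approach was adopted for this feasibility study, which emphasizes descriptive and qualitative feedback". Only cases can supply EMA data. Inclusion and Exclusion Criteria says "The SUDs group will receive the mobile apps, whereas the control group will not", and Limitations acknowledges "the lack of EMA assessments for the control group". Dropout is expected to stay below 40% at 6 months (Statistical Methods, Primary Outcomes).

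In the Discussion, under Anticipated Results, Primary Objectives, the authors forecast: "A degree of correlation higher than 0.70 is expected between EMA data and data collected using other methods". They give no specific value above 0.70.

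**The concern.** Taken literally, the rule rejects a null of rho at or below 0.70. Showing that a correlation exceeds an already high value takes far more data than showing that it exceeds zero, and the sample size was not set with this test in mind. Whether EMA data are valid and reliable is the second of the two primary parameters, and the Dissemination section makes presentation of findings at symposiums conditional on it. If the test fails because the sample is small, the natural report would be that EMA was not reliable, which the data could not support.

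The statistic also has a blind spot. Pearson r does not change when one measure is multiplied by a positive constant. An app that captured the same fraction of every participant's use would score as well as one that captured all of it.

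**Working it through.** **The plan's own figures.** 280 admissions a year over 2 years gives 560, and 80/560 = 14.3%, which matches the stated 14%. No power or precision figure is given for the correlation rule, so there is none to reproduce.

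**Inputs.**
- Null value 0.70, tested at 6 months (Statistical Methods, Primary Outcomes).
- EMA users: 40 (Sample Size; Inclusion and Exclusion Criteria).
- Dropout below 40% at 6 months: 40 × 0.60 = 24 at the ceiling, 40 with no dropout.
- Significance level: assumed 0.05 two-sided. The document states 0.05 only under a secondary outcome and gives no sidedness.
- True rho: not given beyond exceeding 0.70, so a range is shown.

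**Formulas (Fisher z).**
- Critical r = tanh(atanh(0.70) + 1.96/√(n−3))
- Power = Φ((atanh(rho) − atanh(0.70))·√(n−3) − 1.96)
- N for 80% power = ((1.96 + 0.842)/(atanh(rho) − atanh(0.70)))² + 3

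**Critical value**, with atanh(0.70) = 0.867.
- n = 24: 0.867 + 1.96/√21 = 1.295, so r must reach 0.860.
- n = 40: 0.867 + 1.96/√37 = 1.190, so r must reach 0.830.

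**Power.** For example, at rho = 0.80 and n = 24: (1.099 − 0.867) × 4.583 − 1.96 = −0.90, and Φ = 0.18.

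| True rho | n = 24 | n = 40 | N for 80% power |
|---|---|---|---|
| 0.75 | 7% | 9% | 707 |
| 0.80 | 18% | 29% | 150 |
| 0.85 | 43% | 66% | 55 |
| 0.90 | 79% | 96% | 25 |

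Simulation under bivariate normality (100,000 replicates per cell) gives slightly higher values: 20%, 46% and 82% at n = 24, and 31%, 68% and 97% at n = 40, for rho 0.80, 0.85 and 0.90.

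**Sidedness.** One-sided testing lowers the critical r at n = 24 to 0.841. Power at rho 0.80 becomes 28% (n = 24) or 41% (n = 40).

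**All or any.** The rule speaks of several correlations without saying how many must pass. If two had to pass and were independent, power at n = 24 would be 3%, 18% and 63% for rho 0.80, 0.85 and 0.90. Positive dependence would raise these figures.

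**The other reading.** Suppose the rule means that r exceeds 0.70 and differs significantly from zero. At n = 24 an observed 0.70 has a 95% interval of 0.41 to 0.86, so the second condition adds nothing. By simulation, the chance of r above 0.70 at n = 24 is 53%, 72%, 88% and 97% for true rho 0.70, 0.75, 0.80 and 0.85. At rho 0.80 the two readings therefore give 88% and about 18% to 20%.

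**Under-reporting.** If EMA records exactly half of each participant's use, then EMA = 0.5 × use and r = 1, although the mean is wrong by half.

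**The case against.** **This is a pilot and need not be powered.** That is a fair defence of the sample size, which the article describes as descriptive. It does not defend the rule, because the authors themselves tied endorsement to a formal test.

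**The rule can be met.** This stands in part. At a true rho of 0.90 power is 79% to 96%, and 24 is the floor of the range that the plan expects. A reader might infer that endorsement is practically out of reach. That is too strong: the difficulty lies with true correlations up to about 0.80, and at 0.85 the outcome is uncertain.

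**The sentence may mean something milder.** A correlation above 0.70 that is also statistically significant is a possible reading and fits the forecast in the Discussion. If it is what was meant, the power problem goes and one clarified sentence settles it.

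**The Discussion sets a different bar.** A reader might infer a contradiction. The documents do not support that: the Discussion passage is a forecast under Anticipated Results, with the same threshold and direction, and is not a second decision rule. What remains is that results in line with the forecast, such as an observed 0.80, would fail the test at either sample size.

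**CAST covers cannabis only, so its correlation rests on fewer people.** The article does not say that non-users are left out of that correlation. The cannabis share in the Introduction comes from an earlier inpatient study. No smaller number can be derived.

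**Agreement was never claimed.** The plan speaks of strength of association and promises further reliability analyses. The instruments also differ in scale and recall window (12 months, 6 months and 1 month, against 2-week EMA blocks), so an agreement index would not suit CAST. Both remarks are right. Even so, the only stated route to endorsement is Pearson r, and it cannot detect proportional under-reporting even where units could be matched.

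**Conclusion.** The point holds and should be fixed, though it does not undermine the pilot as a whole. As worded, the rule requires an observed r of about 0.86 (n = 24) or 0.83 (n = 40) and would usually deny endorsement to a tool whose true correlation is 0.75 or 0.80. A non-significant result cannot be read as lack of reliability.

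These figures assume a two-sided level of 0.05, roughly bivariate normal data and 24 to 40 evaluable cases. Substance-use data with many zeros would make the Fisher z figures less dependable, and mismatched recall windows would probably lower the correlations. The under-reporting point is algebraic and needs none of these assumptions. How often under-reporting would occur cannot be judged from the document.

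**What to change.** 1. Say which reading is meant. If it is r above 0.70 and significantly different from zero, write that, with the significance level and sidedness. Accept that at n = 24 it would be met about half the time (53%) when the true correlation is only 0.70.
2. Otherwise, replace the yes/no test with each correlation and its 95% confidence interval read against 0.70. EMA is endorsed if the lower bound exceeds 0.70 and not supported if the upper bound is below 0.70. Anything else is inconclusive and used to plan a larger validation study. The bar for endorsement does not move. By the same formula, the inconclusive zone is an observed r of about 0.41 to 0.86 at n = 24, or 0.50 to 0.83 at n = 40.
3. State whether all or any of the correlations must qualify.
4. Where EMA and the comparator share units and can be matched in period, for example RECAP past-month use, add the mean difference with limits of agreement, or an absolute-agreement ICC. For CAST, report correlation alone.

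The cost is a change of wording in the analysis section, with no extra data. The downside is that the pilot may have to report its reliability question as unresolved.

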#### Initial Clinical Assessment and Follow-Up

Participants (i.e., adolescents with SUDs and control subjects) will be approached by a researcher involved in the project (either a clinician specialized in child psychiatry or a master’s level psychologist) who will explain the study and obtain written informed consent from parents or guardian and assent from the adolescent. Participants will be assessed in the week prior to hospital discharge for sociodemographic data, psychosocial information, psychopathology, and substance use (see Variables and Instruments). All youths will be assessed in face-to-face interviews by a specially trained master’s level psychologist at 6-month and 1-year follow-up.

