### Data Analysis

#### Variables and Instruments

Table 1 lists the questionnaires and other assessments that will be used at baseline and at follow-up. The reading level of the questionnaires is grade 6. The questionnaires we plan to use to measure addiction are described below. A combination of self- and clinician-report measures with different time scales (i.e., DEP-ADO, 12 months; CAST, 6 months; RECAP, 1 month) will be used to examine whether EMA data are consistent with information collected in the traditional way. The second type of measures relate to psychopathology with the aim of examining the interplay between substance use and psychiatric disorders.

**Table 1 T1:** **Variables examined in the study**.

Variables	Administration	Initial assessment	Month 6	1 year

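### The comparison of Models A and B does not fix the instrument for follow-up severity: scoring it with either predictor's own method tilts the result toward that method, and functional impairment, a named target, is left out

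*Protocol article*

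**What the plan says.** In the Protocol article, Statistical Methods, Primary Outcomes, baseline severity is expected to "predict the severity of substance use and the level of functional impairment at 1 year", and EMA is expected to do this about as well as the traditional methods. Two simple linear regressions follow. Model A's predictor is severity from EMA; Model B's is severity from self- and clinician-report. On the outcome the text says: "For both the models, the dependent variable will be the severity of SUDs at follow-up". The expected result is: "The estimate of the independent variable is expected not to be lower in the Model A than in the Model B". No margin, test or standardisation accompanies that sentence, and no instrument is named for the outcome.

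Under Variables and Instruments, "Table 1 lists the questionnaires and other assessments that will be used at baseline and at follow-up". DEP-ADO, RECAP, CAST and K-SADS-PL appear at both the initial and the 1-year assessment. EMA has no row. C-GAF is listed at baseline, 6 months and 1 year, as self-report. Follow-up visits at 6 months and 1 year are face-to-face interviews (Initial Clinical Assessment and Follow-Up).

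Two places leave another outcome source open. The Ecological Momentary Assessment section gives, as an example, two-week EMA periods repeated later in the study. The opening line of Outcomes says that information will come from both EMA and questionnaires.

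**The concern.** The comparison is meant to show which baseline measure better predicts the later course. That needs an outcome that does not favour either predictor in advance. If 1-year severity is scored with the instruments that form Model B's predictor, anything stable about those forms (item content, recall style, a consistent way of answering them) adds to Model B's association and not to Model A's. The comparison then partly asks whether EMA agrees with a repeated questionnaire as well as the questionnaire agrees with itself. With an EMA-scored outcome the same happens in reverse.

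At stake is one of the primary validity results. EMA could appear to predict worse, or better, because of how the outcome was scored. A larger sample would not help, since this is bias and not noise.

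The second part needs no such argument. The aim names two 1-year targets, substance-use severity and functional impairment, and the models address only the first.

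**Working it through.** **The plan's own figure.** The protocol gives no power, margin or expected coefficient for this comparison, so there is nothing to reproduce. From Sample Size: 40 cases × 50% retention at 1 year = 20 cases with follow-up. Controls have no EMA (Limitations), so only cases enter Model A. I use n = 20, and n = 40 as the limit with no loss to follow-up.

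**Model (assumed; none of these shares is in the protocol).** Each score has variance 1, split into a true-severity share t, a stable instrument-specific share v, and noise 1 − t − v. EMA and questionnaire have the same t. True severity correlates ρ between baseline and 1 year. The expected standardised slopes are:

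- outcome on Model B's instruments: A = tρ, B = tρ + v
- outcome on EMA (same v): A = tρ + v, B = tρ
- outcome sharing instrument variance with neither: A = B = tρ

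**Outcome on Model B's instruments, t = 0.7, ρ = 0.5.** A = 0.7 × 0.5 = 0.35. B = 0.35, 0.45 and 0.55 for v = 0, 0.1 and 0.2. Share of 40,000 simulated trials in which A is not lower than B:

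| v | n = 20 | n = 40 |
|---|---|---|
| 0 | 50% | 50% |
| 0.1 | 27% | 19% |
| 0.2 | 10% | 3% |

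**Same outcome, t = 0.6, ρ = 0.5.** A = 0.30; B = 0.40, 0.50 and 0.60 for v = 0.1, 0.2 and 0.3. A is lower than B in 68%, 83% and 93% of trials at n = 20, and in 76%, 93% and 99% at n = 40. Varying ρ from 0.3 to 0.7 barely moves the n = 20 results: 68–69%, 83–85% and 92–94%. With an outcome that shares instrument variance with neither predictor, A is lower in about 50%.

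**EMA truly better (80% against 60% true variance), v = 0.25, ρ = 0.5, n = 20.** EMA is not lower in about 10% of runs with the questionnaire outcome, and in about 60% with an outcome from another source.

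**If EMA shares the adolescent's own reporting bias.** Let a fraction f of v belong to the person and so enter EMA as well. Then A = tρ + fv and B = tρ + v. With t = 0.7, ρ = 0.5 and f = 0.5, the slopes are 0.40 against 0.45 (v = 0.1) and 0.45 against 0.55 (v = 0.2). EMA is then not lower in about 37% and 21–22% of runs at n = 20. With f = 1 the tilt disappears (50%).

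**Scale.** On raw scores the slope depends on units: multiplying Model A's predictor by 10 divides its slope by 10 at the same correlation. The percentages above therefore describe a standardised version of the comparison, which the protocol does not state.

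**Functional impairment.** Set side by side, the aim lists severity and functional impairment at 1 year; the model specification lists severity only. Anticipated Results repeats functional impairment as a prediction target, and secondary analysis 6 already uses it as a 1-year outcome. C-GAF is scheduled at that visit.

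**The case against.** A reader might infer that the plan scores follow-up severity with Model B's own questionnaires, and hence that EMA will look worse. The documents do not say so. The instrument is unnamed, later EMA periods and EMA-based outcome information are not excluded, and K-SADS-PL is given at 1 year as a semi-structured interview, a label separate from those that define Model B. The direction of the tilt is therefore not established. Table 1 makes the questionnaire reading the more natural one, but no more than that.

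A reader might also infer that EMA passes or fails on this comparison. For the correlations the protocol does set an endorsement rule at 0.70. For Models A and B it states only an expectation, in a pilot of 80 participants.

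The percentages can be challenged too. They assume standardised slopes, variance shares that nobody has measured here, and in the main case no reporting bias shared by EMA and questionnaires, although EMA is also adolescent self-report. The 50% reference figure itself reflects the lack of a margin, which is a separate matter. All of this stands, and it makes the figures illustrative.

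Finally, a condensed article may leave the scoring of an outcome to a fuller document. That would dispose of a complaint that detail is missing. It does not dispose of this one: the article commits to a single shared severity outcome for two competing measures, scoring it by either measure alone favours that measure, and the omission of functional impairment contradicts the aim in the same section.

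**Conclusion.** The concern holds in conditional form. The protocol does not fix the instrument for follow-up severity. If it is the self- and clinician-report set, as Table 1 suggests, Model B's standardised slope is raised by about the instrument-specific variance share, and an equally valid EMA tends to come out lower. If it is EMA, the tilt reverses by the same amount for the same share. For 10% and 20% shares at n = 20, with a questionnaire outcome, EMA is not lower in about 27% and 10% of runs instead of 50%; the effect shrinks, and can vanish, as EMA shares the adolescent's reporting bias. These sizes rest on assumed shares and on standardised scores. The mismatch between the two-part aim and the single dependent variable rests on the text alone. The change is worth making because this is a primary validity analysis and the remedy uses data already scheduled.

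**What to change.** In Statistical Methods, Primary Outcomes:

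1. Keep Model B's planned combined predictor, and name the instrument or score that defines 1-year severity.
2. Fit both models on the same participants with standardised predictors.
3. Add 1-year C-GAF as a second dependent variable, as the stated aim requires.
4. Add a cross-source check in which predictor and 1-year outcome come from different reporters, for example baseline self-report against 1-year clinician-report, and the reverse.
5. State that any same-instrument result will be read as favouring the method that shares the outcome's instrument.

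The cost is mainly wording, since the measures are already in Table 1 at baseline and 1 year. There are downsides. More than one version of the outcome must be reported. Recall windows will not match fully in the cross-source check (DEP-ADO covers 12 months, CAST 6 months, RECAP 1 month). Some shared-reporter variance may remain, because Table 1 lists C-GAF as self-report and the clinician DEP-ADO itself follows an interview with the adolescent and family.

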##### Psychopathology

The Kiddie-SADS-Present and Lifetime Version (K-SADS-PL) is a semi-structured interview used to assess psychiatric disorders (57).The Affective Reactivity Index (ARI) is a 7-item clinician-reported scale that focuses on distinct domains of irritability (i.e., tonic and phasic), validated in English (58).The Impulsive Behavior Scale (UPPS-P) is a 20-item self-reported scale that focuses on distinct domains of impulsivity (i.e., sensitivity to positive and negative emotions, lack of perseverance, lack of premeditation, and sensation-seeking), validated in French (59).The Adolescent Diagnostic Interview for Borderline Patients (Ado DIB) is a self-reported questionnaire that assesses the diagnostic criteria for borderline personality disorder. Translation and validation in French are provided by Guilé and colleagues (60).Overall functioning will be measured using the Children’s Global Assessment of Functioning (C-GAF), one of the most widely used measures of the overall severity of adolescent disturbance (61).

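### The primary predictive-validity criterion names two 1-year outcomes, but Models A and B test only severity, so EMA is never compared with traditional methods on functional impairment

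*Protocol article*

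**What the plan says.** The Protocol article, Statistical Methods, Primary Outcomes, first states the criterion. Baseline severity of SUDs "should predict the severity of substance use and the level of functional impairment at 1 year", and EMA should do this at least comparably to traditional methods.

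The analysis follows directly: "Two simple linear regression models will be performed". Model A uses severity based on EMA as its predictor, and Model B uses severity based on self- and clinician-report. On the outcome the text is explicit: "For both the models, the dependent variable will be the severity of SUDs at follow-up". The comparison is then worded as an expectation: "The estimate of the independent variable is expected not to be lower in the Model A than in the Model B".

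The measure needed for the second outcome is in the plan. Under Psychopathology: "Overall functioning will be measured using the Children’s Global Assessment of Functioning (C-GAF"), and Table 1 schedules it at the initial assessment, month 6 and 1 year.

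The Discussion (Anticipated Results, Primary Objectives) repeats the expectation about the course of SUDs, with examples: "e.g., in term of persistence, severity, and functional impairment) at least as good as other methods".

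**The concern.** The criterion and the analysis that implements it disagree within a few sentences. The article does not leave the models open for a later document. It fixes their number, predictors, outcome and the expected direction of the comparison. An analysis plan that followed this text would inherit the mismatch.

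At stake is what a favourable Model A would support. Run as written, it could be reported as meeting a criterion that includes functioning when functioning was never examined. EMA could track later substance use well and later functioning poorly, and these two models would not show it. The text also leaves analysts free to decide, after seeing the data, whether one outcome or two should count.

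**Working it through.** The document gives no figure to reproduce, so the check is a count and a comparison of sections.

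**Step 1. Models needed and models planned.**
- Outcomes in the criterion: 2 (severity of substance use; functional impairment), both at 1 year.
- Predictors compared: 2 (EMA-based severity; severity from self- and clinician-report).
- A simple linear regression has one predictor and one outcome, so models needed = 2 × 2 = 4.
- Models planned = 2, both on severity.
- Shortfall = 4 − 2 = 2, namely the pair with functional impairment as outcome.

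This treats severity of substance use (criterion) and severity of SUDs (models) as the same outcome.

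**Step 2. Whether another analysis fills the gap.**
- Pearson correlations (Statistical Methods, Primary Outcomes): EMA against questionnaires on substance use at 6 months. Functioning is not involved.
- Secondary item 2: functional impairment compared between participants with and without SUDs at baseline. There is no EMA comparison.
- Secondary items 3 and 4: onset, persistence or cessation of SUDs predicted from clinical and psychosocial features. There is no EMA comparison.
- Secondary item 5: mixed-effect models of EMA data on substance use, symptoms and stressors. There is no comparison with traditional methods.
- Secondary item 6: functional impairment at 1 year is an outcome, but the predictor is level of app use. Baseline severity is not a predictor, and EMA is not set against traditional measurement.

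EMA-versus-traditional analyses of functional impairment: 0 of the 2 models needed.

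**Step 3. Whether the comparison can simply be copied to the C-GAF.** In a simple regression, slope = r × SD(Y) / SD(X). With both predictors standardised and the same participants, SD(X) = 1 and SD(Y) is common, so comparing slopes is comparing correlations. Without standardisation, the slopes also reflect the units of each predictor.

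The sign matters as well. The document does not state which way the C-GAF is scored. Suppose higher means better functioning and, as assumed values, EMA correlates −0.2 and the traditional measure −0.5 with it. Since −0.2 > −0.5, the EMA estimate is not lower, and the weaker predictor satisfies the wording. With the scale reversed, 0.2 < 0.5 and it does not. The scoring direction must therefore be fixed before the wording is applied to functioning.

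**The case against.** The strongest reply is that this is a feasibility study with a descriptive emphasis. The Outcomes section defines EMA validity through correlations and does not list prediction. The only explicit endorsement rule is the 0.70 correlation threshold. For Models A and B the text states an expectation, with no margin or test. All of this is correct and limits the weight of the point. A reader might infer that the protocol contains a formal rule under which EMA would be declared as good as traditional methods; it does not.

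Three further readings go too far.
- A reader might count the Discussion's list, which adds persistence, as another definition of the criterion. It is introduced as a set of examples under anticipated results and defines nothing.
- A reader might say that the follow-up time of the models is open. The criterion two sentences earlier says 1 year, and the Discussion refers to the 1-year follow-up.
- A reader might say that functional impairment is not analysed at all. Secondary items 2 and 6 both use it; what is missing is the EMA-versus-traditional comparison.

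What does not fall away is the mismatch itself. The criterion stands under the primary outcomes in Statistical Methods, names two outcomes, and is followed by models for one.

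**Conclusion.** The point holds as an internal inconsistency in the Protocol article, Statistical Methods, Primary Outcomes. One of the two named 1-year outcomes is modelled, and neither of the two regressions needed for functional impairment is planned there or elsewhere. The conclusion rests on reading the text and on equating severity of substance use with severity of SUDs.

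It is tempting to give the size as a probability that EMA meets the comparison on one outcome or on two. The documents do not support that. Such a figure would depend on assumed correlations, and largely on the absence of a margin with about 40 × 0.50 = 20 SUD participants expected at 1 year. Those are separate features of the plan. Nor do the documents say that both outcomes must be met together.

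The correction is worth making before analysis because it decides what may be claimed about EMA and functioning. It does not affect the sample size, the correlation analysis or the feasibility outcomes.

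**What to change.** Amend Statistical Methods, Primary Outcomes, in one of two ways.

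1. **Test both outcomes.** State that Models A and B will each be fitted for two dependent variables at 1 year: severity of substance use, and functional impairment (C-GAF). Standardise the predictors. Code the C-GAF so that higher means worse, or compare the absolute strength of association. Report each outcome separately and claim comparability only for the outcome on which it was tested.
2. **Narrow the criterion.** Remove functional impairment from it and limit the conclusion to severity of substance use.

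In either case, keep the examples in the Discussion consistent with the choice.

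The first option costs two extra regressions on data already scheduled for collection, and the conclusion may be less favourable. The second costs only wording, at the price of a narrower claim.
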